#### Secondary end points

The secondary end point is aneurysm growth on follow-up imaging. Recruiting units will record if patients have undergone follow-up imaging. Aneurysm growth will be recorded if there was any clinically observable growth, in the opinion of a consultant neuroradiologist or an MDT, when directly comparing baseline and follow-up scans.

### Data transmission and editing

The recruiting units will populate two data sheets, one containing patient identifiable details required for hospital admission database searches and a second containing clinical details only. These two spreadsheets will be cross-referenced using an aneurysm-level pseudonymisation number contained in both spreadsheets. Recruiting units will send each data sheet to the coordinating unit separately through a 256-bit end-to-end encryption service.

The requirement for editing the data will be minimised through the use of restricted fields and predefined lists of valid codes for each element on the datasheet. All queries and discrepancies raised by the coordinating centre regarding the data entry will be submitted to the respective recruiting units through a single query sheet referencing the pseudonymisation number.

### Sample size

There are no accepted methods for power calculation for validation studies of prognostic models. Earlier methods included the rule of thumb to have 10 events for every covariate tested, however, more modern methods for minimum sample size calculation have been proposed by Riley *et al.*^17^ The online package *pmsampsize* uses the method by Riley *et al* to estimate the minimum sample size. Using figures from our feasibility work (2124 patients with 60 rupture events over 4010 patient years), estimating 28 df and varying Cox-Snell R^2^ value d from 0.03 to 0.05 resulted in a minimum sample size ranging from 5143 to 8559. The number of df allows for all categorical variables as well as continuous variables such as patient age or aneurysm size which may require polynomial equations.

The method by Riley *et al* is yet to be widely used and does not consider the prevalence of uncommon variables such as ADPKD. The older rule of thumb requiring 10 events per covariate was therefore also considered. For the first objective, the 6 covariates in the PHASES score will be tested suggesting at least 60 SAHs will need to be captured. ISUIA recorded 51 ruptures in 1692 patients over 4.1 years. Sixty events may therefore be expected in 1990 patients with 8161 years of follow-up. For the second objective, 120 events will need to be observed to account for the six additional commonly occurring covariates which would be expected in 3981 patients with 16 332 years of follow-up.

However, the 10 events per covariate rule of thumb does not consider the prevalence of the covariate in the study population. Therefore, rarely occurring populations may have insufficient data to estimate risk. ADPKD is one such population and including it as a covariate requires a larger study size. In ADPKD, 10 events are expected in 1360 patient years of follow-up assuming the risk of SAH is similar to the general population. However, 16 332 years follow-up would only yield 195 years in patients with ADPKD (based on a population study which found 53/4436 patients with UIA had ADPKD).^18^ Therefore, 113 905 years of follow-up would be required to capture 10 ruptures among 1340 years follow-up in patients with ADPKD. This equates to a total cohort of 22 781 patients.

The Transparent Reporting of a multivariable Prediction model for individual Prognosis or Diagnosis (TRIPOD) guidelines highlight the lack of consensus of how to calculate a sample size and suggest aiming for larger sample sizes which give more precise and reliable results. Smaller sample sizes are at risk of performance optimism. Therefore, the ROAR study will aim to collect 20 000 patients. Based on feasibility studies, this is the maximum practical sample size, and power calculations show that it is sufficient to generate precise estimates and account for all covariates.

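### The protocol says 20 000 patients suffices for all covariates, but its own ADPKD calculation asks for 22 781 at an unstated 5 years of follow-up each

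*Protocol article*

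**What the plan says.** All the figures come from the Sample size section of the protocol article, which proceeds in four steps.

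- **Modern method.** A *pmsampsize* calculation based on feasibility data gives 5143 to 8559 patients. The section adds that this method takes no account of how rare a covariate such as ADPKD is.
- **Rule of thumb, common covariates.** "The older rule of thumb requiring 10 events per covariate was therefore also considered". The planning input is that "ISUIA recorded 51 ruptures in 1692 patients over 4.1 years". This leads to 1990 patients for the six PHASES covariates (60 events) and 3981 patients for twelve covariates (120 events).
- **Rule of thumb, ADPKD.** "In ADPKD, 10 events are expected in 1360 patient years of follow-up assuming the risk of SAH is similar to the general population". With 53 ADPKD patients among 4436 patients with an unruptured aneurysm, the section arrives at 113 905 patient-years in total, and then: "This equates to a total cohort of" 22 781 patients.
- **Target.** After citing the TRIPOD guidance, "the ROAR study will aim to collect 20 000 patients". Feasibility work is said to show that "this is the maximum practical sample size", and the paragraph closes with the statement that "power calculations show that it is sufficient to generate precise estimates and account for all covariates".

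The Study setting section describes a separate ADPKD-enriched cohort from renal units. The Sample size section does not count it.

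**The concern.** The closing statement covers all covariates, and the section treats ADPKD as a covariate to be included. Yet the one calculation that deals with ADPKD gives a cohort larger than the target. The *pmsampsize* range cannot fill the gap, because the section itself says that the method ignores the prevalence of uncommon variables. No printed calculation therefore supports the sentence where ADPKD is concerned.

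The conversion from patient-years to patients also changes its follow-up assumption without notice, so a reader cannot tell which follow-up the plan relies on.

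At stake is how the ADPKD estimate will be read. The strengths list at the front of the article names ADPKD as a rare group that the large cohort makes it possible to include. A reader would take the ADPKD coefficient as shown to be adequately informed, when the printed arithmetic does not show that.

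**Working it through.** **Inputs (Sample size section).** 51 ruptures in 1692 patients over 4.1 years; 10 events per covariate; ADPKD share 53/4436; target 20 000.

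**1. Reproduce the earlier figures.**
- Rate = 51 / (1692 × 4.1) = 0.00735 per patient-year.
- 60 events: 60 × 1692/51 = 1990.6 patients and 60/0.0073517 = 8161 patient-years. Both match.
- 120 events: 120 × 1692/51 = 3981.2 patients. This matches. The patient-years come to 16 322 or 16 323, against 16 332 printed, which is a small slip without consequence.
- Both cohort sizes therefore use 4.1 years per patient.

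**2. Reproduce the ADPKD figure.**
- ADPKD years for 10 events: 10/0.0073517 = 1360.
- ADPKD years in 16 332 patient-years: 16 332 × 53/4436 = 195.
- Total patient-years: 1360 × 16 332/195 = 113 905, an exact match. With 1340, which is printed later in the same paragraph, the result would be 112 230, so 113 905 belongs to 1360.
- Cohort: 113 905/22 781 = 5.000 years per patient. The conversion uses exactly 5 years.
- At 4.1 years: 113 905/4.1 = 27 782 patients.

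**3. Compare with the target.**
- 1 − 20 000/22 781 = 12.2% short.
- 1 − 20 000/27 782 = 28.0% short.

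**4. Expected ADPKD ruptures with 20 000 patients.** Events = 20 000 × f × (53/4436) × 0.0073517, where f is mean follow-up in years.

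| Mean follow-up f | Total patient-years | ADPKD patient-years | Expected ADPKD ruptures |
|---|---|---|---|
| 4.1 | 82 000 | 980 | 7.2 |
| 5 | 100 000 | 1195 | 8.8 |
| 5.7 | 113 900 | 1361 | 10.0 |
| 8 | 160 000 | 1912 | 14.1 |

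The break-even is 113 905/20 000 = 5.695 years. The 5.7 row uses 5.695. The 8-year row is an assumption, discussed with the objection.

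**5. Effect on precision.** The approximate 95% interval for the ADPKD hazard ratio extends by a factor of exp(1.96/√events) either way, treating the comparison group as large. That is 1.86 with 10 events, 1.94 with 8.8 and 2.08 with 7.2.

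**The case against.** **Patient-years bind, not patients.** This is the strongest reply, and it stands. Patients are identified from documents dated 2006 to 2020. Baseline collection is planned to end on 31 July 2023, and patients without treatment or death are censored at database submission (Study design). If submission follows that date, administrative follow-up runs from about 2.6 to 17.6 years. Under uniform identification the mean is (2.6 + 17.6)/2 = 10.1 years. If the roughly 20% who are treated (Discussion) contributed nothing, it would be 0.8 × 10.1 = 8.1 years before deaths. Shorter search windows at some units and deaths would lower this. A mean above 5.7 years is therefore plausible, though it rests on assumptions the article does not make. Hence a reader might infer that the ADPKD estimate will be under-informed; the documents do not support that.

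**A harsher scenario is tempting.** The feasibility data average 4010/2124 = 1.89 years. At the planning rate, that would give only 3.3 ADPKD ruptures in 20 000 patients. This reading should not be used. The article uses those data for the *pmsampsize* run ("Using figures from our feasibility work") and nowhere offers them as the study's expected follow-up. The value is also shorter than the 2.6-year administrative minimum above. Mixing sources cuts the other way too: the feasibility rate of 60/4010 = 0.01496 per year gives 14.7 to 17.9 ADPKD ruptures at 4.1 to 5 years.

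**The rate may be conservative.** ADPKD is assumed to carry general-population risk, while the Introduction lists it among features associated with rupture or thought to predispose to it. At 5 years, a relative risk of 10/8.8 = 1.14 would already give 10 events. This is fair, but the protocol's calculation does not claim it.

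**ADPKD is not the sole reason for the target.** Correct: the target follows from the TRIPOD advice and practical limits. The separate renal-unit cohort may also add ADPKD events, but the sufficiency sentence does not rely on it.

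Together these replies show that 20 000 may be enough. They do not show that the article's calculations establish it, and that is what the sentence says.

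**Conclusion.** The point holds as a defect in the stated justification. For ADPKD, the sufficiency statement is contradicted by the section's own result: the target is 12% below the printed requirement, and 28% below it if the 4.1 years of the preceding steps is kept. At the planning rate and prevalence, the expected count is 7 to 9 ADPKD ruptures instead of 10.

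The practical effect is modest. The interval factor for the ADPKD hazard ratio moves from about 1.9 to at most about 2.1, and the shortfall disappears if mean follow-up reaches about 5.7 years.

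The conclusion rests on the protocol's own rate, prevalence, 10-event rule and follow-up values. It does not extend to the rest of the model: 20 000 exceeds both the 5143 to 8559 range and the 3981 for the common covariates. Nor does it show that the design is too small.

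**What to change.** - State one assumed mean follow-up per patient, justified from the identification window, the expected submission date, and losses to treatment and death. Use it for every cohort size in the section.
- Then do one of two things. Either show that 20 000 patients deliver 113 905 patient-years, which needs a mean of about 5.7 years or more. Or limit the sufficiency statement to the common covariates and report the expected ADPKD ruptures at 20 000 as a range over follow-up (7.2 at 4.1 years, 8.8 at 5 years, 10 at about 5.7 years), noting that the separate ADPKD-enriched cohort is not counted.
- Correct 1340 to 1360 ADPKD patient-years, the value to which 113 905 corresponds.

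This changes text only. It needs no extra patients, data or analyses. The cost is a slightly less favourable claim for ADPKD if the second route is taken.

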### Statistical analysis

#### Objective 1: PHASES validation

The PHASES study provides the coefficients from their Cox regression model and baseline survival at 5 years which allows the absolute 5-year risk of rupture to be calculated for all patients who are not censored before 5 years. Time to censoring will be calculated (whichever is soonest of the date of treatment, date of death or the HES/PEDW/SMD search date) to ensure 5 years of follow-up if rupture has not occurred. Discrimination will be assessed using Harrell’s C-index of concordance and Royston and Sauerbrei’s D statistic. Calibration will be assessed at the 5-year time point using the method by Royston.^19^ These will be used to calculate the number of SAH events per 5 years for each PHASES score (≤2 to 12+) and expressed as a percentage with 95% CI to compare with the PHASES estimates.

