### Study design

The Risk of Aneurysm Rupture (ROAR) study is a longitudinal study that uses a hybrid design of patient identification at regional neurosurgical units and prospectively collected national hospital admissions databases for outcome events. The study will establish a cohort of patients with a UIA and measure how many subsequently ruptured. This observed rupture rate can be compared with a rate estimated by the PHASES score to determine its accuracy.

Each neurosurgery unit in the UK will be invited to search their medical records for patients diagnosed with a UIA. This search method will be tailored by the individual neurosurgery unit based on what records they keep, but search strategies may include: multidisciplinary team (MDT) meeting logs, radiology reports or electronic patient records. The search strategy will be predefined by individual units dependent on their record systems. The maximum date range for identifying patients is documents dated 1 January 2006 to 31 December 2020, however, this period may be shorter for each unit depending on availability of records. Whatever date range is chosen by the unit, it will be predefined and if the patient’s UIA was newly diagnosed during this period it will be classed as *new* and those who were diagnosed before this period but identified from a document during the aneurysm follow-up will be classed as *follow-up*, and their recruitment date recorded as the date of the document from which they were identified. This will minimise the prevalence-incidence (Neyman)^14^ selection bias created by identifying patients diagnosed before the unit’s search period but who survive without rupture to make it into the search period, whereas their counterparts diagnosed at the same time who rupture and die are not identified. It will also allow comparison of rupture risk of newly diagnosed aneurysms and those with known diagnoses. Baseline clinical characteristics and aneurysm characteristics will be collected as per the common data elements for UIA research.^15^ All data collectors will undergo training in coding data elements delivered by the coordinating centre. Collecting baseline data from local medical records allows deeper phenotypic typing and higher data fidelity than using national admission databases.

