#### Objective 3: long-term rupture rates

All patients, including those who underwent aneurysm occlusion, will be included in time-to-event analysis which will cover the whole duration of available follow-up. This will include Kaplan-Meier and proportional hazards models for univariate and multivariate survival curve fitting. A cumulative hazard plot will be used to assess if rupture risk is constant or varies with time from diagnosis.

Once the cohort is established, funding will be sought for repeated searches at regular intervals (5 yearly) to update models and provide progressively long-term rupture rates.

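### Objective 1's 5-year completeness rule keeps early ruptures but drops non-ruptured patients censored early, which raises observed rupture risk above a censoring-aware estimate

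*Protocol article*

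**What the plan says.** Under Objective 1: PHASES validation, the protocol article takes the Cox coefficients and 5-year baseline survival from PHASES, "which allows the absolute 5-year risk of rupture to be calculated for all patients who are not censored before 5 years". Time to censoring is "whichever is soonest of the date of treatment, date of death or the HES/PEDW/SMD search date", and its stated purpose is "to ensure 5 years of follow-up if rupture has not occurred". Discrimination is by Harrell's C and the D statistic. On calibration: "Calibration will be assessed at the 5-year time point using the method by Royston". The output compared with PHASES is then described: "These will be used to calculate the number of SAH events per 5 years for each PHASES score", as a percentage with a 95% CI.

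Objective 3 is worded differently: "All patients, including those who underwent aneurysm occlusion, will be included in time-to-event analysis". Objective 1 has no such statement.

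On the calendar, Study design says: "The maximum date range for identifying patients is documents dated 1 January 2006 to 31 December 2020". The same section has baseline data collection ending on 31 July 2023 and results no sooner than 31 July 2024. Patients without an earlier censoring event are censored on the day the cohort is submitted to the databases. That day is not given.

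**The concern.** Five years of follow-up is demanded only of patients who have not ruptured. Those who rupture stay in however short their follow-up. Those who do not rupture but are censored early leave both the numerator and the denominator, and their event-free time is lost. The resulting percentage is ruptures divided by ruptures plus patients event-free at 5 years, which is not a 5-year risk.

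The restriction gains nothing. A PHASES prediction needs only baseline values and the published baseline survival, so it exists for every patient. The named performance measures accept censored observations.

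Validating PHASES is the first objective, and the Discussion expects the study to settle the score's validity. An upward shift in observed risk goes straight into the observed/expected ratio, and a cohort of 20 000 does not shrink it.

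**Working it through.** **Inputs from the protocol article.** ISUIA: 51 ruptures in 1692 patients over 4.1 years (Sample size). Rupture rate 1.4% per year (Introduction). UK treatment rate about 20% (Discussion). Identification window 1 January 2006 to 31 December 2020, and the two 31 July dates above (Study design).

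**Assumptions not in the document.** Entry uniform over the window; search in mid-2023 or mid-2024; constant rupture hazard; censoring independent of rupture; treatment either early (exponential, mean 0.5 years) or uniform over 5 years; non-rupture death 0-3% per year.

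**The plan's own figures.** It states no figure for this bias. Its Objective 1 size reproduces: 60/51 × 1692 = 1990.6 patients, and × 4.1 = 8161 years. The rate behind it is h = 51/(1692 × 4.1) = 0.735% per year.

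**True 5-year risk.** 1 − exp(−5h) = 3.61% at 0.735% per year and 6.76% at 1.4% per year.

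**Risk under the rule.** Let E be the proportion seen to rupture by 5 years and S the proportion followed event-free to 5 years. The rule gives E/(E + S). Nobody in that set is censored before 5 years, so Kaplan-Meier computed on it at 5 years equals the same proportion.

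**Search date only, by hand, h = 0.735%.**
- Mid-2023: follow-up runs from 2.58 to 17.58 years, so (5 − 2.58)/15 = 16.1% of entrants can be counted only if they rupture. S = 0.839 × 0.9639 = 0.808. E ≈ 0.839 × 0.0361 + 0.161 × [1 − exp(−0.00735 × 3.79)] = 0.0303 + 0.0044 = 0.0347. E/(E + S) = 4.12%, ratio 1.14.
- Mid-2024: (5 − 3.58)/15 = 9.5%. S = 0.905 × 0.9639 = 0.873. E ≈ 0.0327 + 0.095 × 0.0310 = 0.0356. E/(E + S) = 3.92%, ratio 1.09.

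**With treatment and death, by simulation (2 million patients per scenario).**

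| Search | Censoring | True 3.61% reads as (ratio; kept) | True 6.76% reads as (ratio; kept) |
|---|---|---|---|
| mid-2023 | search date only | 4.12% (1.142; 84%) | 7.67% (1.135; 85%) |
| mid-2023 | + 20% treated early | 4.21% (1.168; 68%) | 7.86% (1.163; 68%) |
| mid-2023 | + 20% early, death 2%/year | 4.41% (1.223; 61%) | 8.29% (1.226; 62%) |
| mid-2023 | + 20% uniform, death 3%/year | 5.03% (1.394; 59%) | 9.27% (1.371; 59%) |
| mid-2024 | search date only | 3.92% (1.087; 91%) | 7.32% (1.083; 91%) |
| mid-2024 | + 20% early, death 2%/year | 4.22% (1.169; 66%) | 7.87% (1.164; 66%) |
| mid-2024 | + 20% uniform, death 3%/year | 4.74% (1.313; 63%) | 8.85% (1.309; 64%) |

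Kaplan-Meier on all patients gave 3.58-3.64% and 6.74-6.80% throughout, which recovers the truth.

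**Informative treatment.** Hazard 1.4% per year, gamma frailty, treatment probability proportional to unmeasured risk, early treatment, mid-2023 search, death 2% per year:

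| Frailty variance | True | Kaplan-Meier, all patients | Under the rule |
|---|---|---|---|
| 0.5 | 6.7% | 6.0% | 7.3% |
| 1 | 6.5% | 5.2% | 6.5% |
| 2 | 6.3% | 4.2% | 5.3% |

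The rule lies above Kaplan-Meier each time, but not always above the truth.

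**The case against.** **The naive proportion is not written out.** The sentence on patients not censored before 5 years concerns predicted risk. No sentence says that patients leave the C, D or calibration analyses, and the percentages are said to come from those time-to-event methods. The article is also a condensed account. This lowers certainty about what will be done, but it does not rescue the text: the article states both the restriction and its purpose, and censoring-aware methods help only if the censored patients are supplied to them.

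**A reader might infer that PHASES will appear to under-predict.** The document does not support that. At 1.4% per year, the rate the Introduction cites to the same source as PHASES, 5-year risk is about 6.8%. If the UK truth were 3.6% and read as 4.4%, then, ignoring case mix, PHASES would still look too high. The rule shifts the ratio without fixing the conclusion.

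**A reader might infer that the net bias always runs upward.** Only the shift relative to a censoring-aware estimate does. The Discussion concedes that some treatment selection cannot be eliminated. In the informative scenarios the rule's answer matched or fell below the truth at the two larger frailty variances, where plain Kaplan-Meier was further off. That cancellation is accidental and cannot be relied on.

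**A reader might infer a distorted calibration slope,** from more early treatment at high scores. The document gives no treatment rate by score or size. The inflation is nearly the same at both hazards, and early treatment adds little to it, so this is not claimed.

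**A reader might infer far larger inflation from the feasibility data,** with mean follow-up 4010/2124 = 1.9 years. The Discussion expects follow-up of up to 15 years, so that does not carry over.

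**Conclusion.** The point stands as a fault in the Objective 1 wording: the rule conditions the analysis set on the outcome and raises observed 5-year risk, and the observed/expected ratio, relative to a censoring-aware estimate on all patients. It could produce apparent under-prediction by PHASES or conceal over-prediction.

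The size is about +8% to +14% from the search date alone and about +16% to +23% with 20% early treatment and 2% per year death. The range is about 1.08 to 1.39 over the scenarios examined. These figures rest on uniform entry, a search between mid-2023 and mid-2024, constant hazard, independent censoring, and assumed treatment timing and death rates. Units may also use shorter identification windows, which would change the entry pattern. The direction of the net error against the truth is not established if treatment is informative.

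**What to change.** In Objective 1, delete the 5-year completeness restriction and state that:

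- PHASES predicted 5-year risk is computed from baseline values for every eligible patient.
- Observed 5-year risk per score group is 1 minus Kaplan-Meier at 5 years, with 95% CI, on all eligible patients, censoring at treatment, death and search date as the protocol already defines.
- C, D and the calibration assessment use the same full set.
- A sensitivity analysis reports cumulative incidence with death as a competing event.

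A censoring-weighted analysis using baseline variables related to treatment is an optional further sensitivity analysis. It can address only selection explained by measured variables.

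The cost is a change of wording before analysis starts. No new data are needed, and the 34-39% of patients discarded in the central scenarios return to the analysis.
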